#### Process Measures Evaluation

PWG facilitators keep a journal to capture evidence about the process of implementation, such as the number of women attending the meeting and their timing, areas of discussion, key learnings, other community members and organizations involved. In addition, regular communication with project managers and through the closed facebook group will allow the facilitators to discuss any issues and gain support from others.

Empowerment of women who are members and facilitators of the PWGs in each community is measured at the onset of the process (at the start of the intervention planning phase in each service), and at the end of the intervention period. This is done through the administration of the GEM, both the Emotional Empowerment Scale (EES) and the 12 Scenarios to measure the empowerment process (22). In addition, satisfaction with the PWG process, implementation and experience of the intervention and outcomes are evaluated using semi-structured interviews at the completion of the study. Participants include PWG participants and facilitators, along with some health care providers and community women who have not been involved in the women's groups. Around 10 interviews will be performed for each participating community.

GEM tool data is collected in hard copy, entered electronically by a member of the investigator team and original data kept in a locked cabinet at the sponsor organization. Data entered is cross checked by another investigator to increase the accuracy of data entry and coding. Digitally recorded qualitative interview data is transcribed as word documents. The team has developed a protocol to manage the de-identification and cross checking of qualitative data with respondents. This includes the creation of a flow chart for qualitative data management, standardization of file naming conventions, agreed de-identification processes and cross checking with other members of the investigator team.

The process evaluation strategy is based on robust strategies for evaluating complex interventions, aiming to develop a programme theory for the intervention (48). For process evaluation measurement using the GEM tool, pre and post GEM scores are analyzed using bivariate descriptive statistics. Qualitative evaluation of the process and outcomes using detailed interviews and observation via facilitator journals will uncover how participatory groups and individuals are able to produce and sustain change in MCH care, neglected in previous studies of women's group interventions. Qualitative data (journals and interviews) are transcribed in full. Transcripts are entered into NVivo and abductive coding (49) will first group the findings and do a line by line coding under each question and then inductively identify themes from the data using constant comparison. Analysis of the qualitative data is led by Aboriginal and Torres Strait Islander investigators. The combined findings will be used to generate an explanatory theory about how and why the intervention works (or otherwise) in a variety of contexts. In doing this we will integrate qualitative themes derived from trial data with Aboriginal and Torres Strait Islander knowledge frameworks and concepts (50).

#### Economic Evaluation

A cost-consequence analysis (CCA) and cost-effectiveness analysis (CEA) will be undertaken from the health funders perspective. Costs for the CCA and the CEA will be obtained from the trial data, and include all training (including annual meetings), staff time and resource use costs to the health system for a hypothetical nation-wide roll-out of the program. The outcomes for the CCA will be all primary and secondary outcomes for the study. The outcome for the CEA will be change in mean birthweight (as the main direct health outcome measure). The analysis will identify the incremental cost-effectiveness ratio (ICER) of a nationwide roll-out of the WOMB intervention compared to standard care. A budget impact analysis, that captures the impacts of the intervention on expenditure of the Federal and state governments, and individuals over a 5 year time frame, will also be undertaken.

Data management procedures for the economic analysis will follow the same process as primary and secondary outcome data and will be cross checked in consultation with health economists on the investigator team.

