This study examines whether PWGs, as an intervention, improve the quality of Indigenous MCH care. More specifically, it will determine the effectiveness of PWGs in improving quality of care and intermediate health and well-being outcomes in MCH; the cost-effectiveness of PWGs for improving quality of MCH care; the degree to which the PWGs are associated with a change in empowerment measured using the global empowerment measure (GEM) scores for women involved (22); and the processes through which PWGs exert effects in various contexts.

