## Research Question and Objectives

Do participatory women's groups (PWGs), as an intervention, improve the quality of maternal and child health (MCH) care in Australian Indigenous primary health care (PHC) services?

The objectives are to determine:

The effectiveness of PWGs in improving quality of care and intermediate outcomes in MCH;The cost-effectiveness of PWGs for improving quality of MCH care;The degree to which the PWGs are associated with a change in global empowerment measure (GEM) scores for participating women; andHow and why PWGs exert their effects in various contexts.

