**Figure 1 F1:**
[figure not shown]
Stepped wedge design and participant timeline.

Secondary outcomes: Secondary outcomes will include: (i) percentage of pregnant women having their first antenatal visit before 13 weeks gestation; and (ii) mean birthweight.

Process measures include changes in empowerment for PWG members [measured using the validated Growth and Empowerment Measure (GEM)] (22), alongside a theory-generating process evaluation using qualitative methodology informed by Indigenist and critical theory of the implementation and experience of the intervention (42, 43).

A cost-consequence analysis (CCA) and cost-effectiveness analysis (CEA) will be undertaken from the health system perspective. The outcomes for the CCA will be all primary and secondary outcomes for the study. The outcome for the CEA will be a 100 g increase in mean birthweight (as the main direct health outcome measure).

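### The second objective asks for cost-effectiveness in improving quality of care, but the only planned cost-effectiveness ratio is per unit of birthweight

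*Protocol article*

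**What the plan says.** The aim is stated twice. The end of the Introduction lists "the cost-effectiveness of PWGs for improving quality of MCH care" among the things the study will determine, and Research Question and Objectives repeats it as the second objective: "The cost-effectiveness of PWGs for improving quality of MCH care".

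The analysis is also stated twice. In the Outcomes section, after Figure 1: "The outcome for the CEA will be a 100 g increase in mean birthweight (as the main direct health outcome measure". In Economic Evaluation: "The outcome for the CEA will be change in mean birthweight (as the main direct health outcome measure". The latter section plans one ratio: "The analysis will identify the incremental cost-effectiveness ratio (ICER) of a nationwide roll-out of the WOMB intervention compared to standard care". The QCI comes in through a separate analysis: "The outcomes for the CCA will be all primary and secondary outcomes for the study".

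The Outcomes section makes change in the QCI the primary outcome and lists mean birthweight as the second of two secondary outcomes. The two descriptions of the economic analysis also name the perspective differently: "undertaken from the health system perspective" and "undertaken from the health funders perspective".

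**The concern.** The objective and the analysis meant to serve it name different effects. The protocol distinguishes a CCA, which lists costs and outcomes side by side, from a CEA, which yields a ratio. It attaches the term cost-effectiveness analysis to birthweight alone. This is not a detail left for a later analysis plan to supply, because the article itself fixes the CEA outcome, in two places.

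At stake is whether the trial can report a cost per unit of improvement in the quality of care it sets out to change. The Introduction motivates the study partly by the lack of cost-effectiveness evidence covering both service provision and health outcomes. The planned ratio covers only the second. Data Collection, Management and Analysis is also more confident about quality of care than about birthweight: it regards the follow-up as long enough to show effects on the former and only possibly on the latter. The sole ratio thus rests on the outcome that the protocol is less sure will move.

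**Working it through.** **Objective against analysis.** No arithmetic is needed for the main point.

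| Element | Effect measure |
|---|---|
| Second objective, and the aim in the Introduction | Quality of MCH care |
| Primary outcome | QCI, the trial's measure of quality of care |
| CCA | All primary and secondary outcomes, so QCI included; no ratio |
| CEA, Outcomes section | 100 g increase in mean birthweight |
| CEA, Economic Evaluation | Change in mean birthweight |
| ICERs planned | One |

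The two birthweight wordings are compatible if 100 g is the unit of the ratio, which is the likely meaning. Neither gives a ratio per unit of QCI.

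**Precision of the birthweight denominator.** Inputs from Sample Size: 10 services, 20 records each (200 in total), five steps, intracluster correlation 0.15, two baseline audits and one subsequent audit, QCI SD 13.58, a 5-point change, alpha 0.05 (taken as two-sided), design effect 0.40, power 99%. For birthweight the section gives only the 100 g difference. It states no SD, intracluster correlation or power.

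1. Reproduce the design effect with k = 5, b = 2, t = 1, n = 20, ρ = 0.15:
 [1 + ρ(ktn + bn − 1)] / [1 + ρ(0.5ktn + bn − 1)] × 3(1 − ρ) / [2t(k − 1/k)]
 = (21.85 / 14.35) × (2.55 / 9.6) = 0.404. The stated value is 0.40.
2. Equivalent unadjusted sample: 200 / 0.40 = 500, or 250 per condition.
3. Reproduce the QCI power: SE = 13.58 × √(2/250) = 1.21 points. 5 / 1.21 = 4.1 SEs, so power is Φ(4.12 − 1.96) = 98.4%. The stated value is 99%, so the basis reproduces.
4. Use the same basis for a true 100 g difference, with SE = SD × √(2/250), power = Φ(100/SE − 1.96), and probability of a zero or negative estimate = Φ(−100/SE). The SD is an assumption, and carrying over the design effect of 0.40 applies the QCI's intracluster correlation to birthweight:

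| Assumed SD | SE | Power | Estimate zero or negative |
|---|---|---|---|
| 400 g | 35.8 g | 80% | 0.3% |
| 500 g | 44.7 g | 61% | 1.3% |
| 600 g | 53.7 g | 46% | 3.1% |

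5. Solving for the SD, 80% power needs an SD of about 399 g or less.
6. Sensitivity to the intracluster correlation: values from 0 to 0.15 move the design effect between 0.31 and 0.43. At an SD of 500 g, power then lies between about 57% and 72%.

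The Sample Size sentence on birthweight says that a 100 g difference would be significant. On this basis an observed 100 g reaches p < 0.05 if the SD is about 570 g or less (100 / (1.96 × √(2/250))). At that SD, power for a true 100 g is only 50%. The sentence is a significance threshold, not a power statement.

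**The case against.** The strongest reply is that the CCA already sets incremental cost beside the change in QCI. Both inputs to a cost-per-QCI figure are planned, and only the division is missing. The Abstract also uses a single cost-effectiveness label for the economic work, so the second objective could be read as a heading over the CCA, CEA and budget impact analysis together. This stands in part. A reader might infer that the objective goes unanswered, and the documents do not support that. What is absent is a ratio, not all economic evidence on quality of care.

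Birthweight is also a reasoned choice. The protocol calls it the main direct health outcome, and a ratio on a health outcome is easier to set against other programmes. That stands as a reason to keep the birthweight ratio and not to demote it. It does not explain why the effect named in the objective has no ratio.

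A reader might go further and call birthweight underpowered as a fact. The documents give no SD, so the statement can only be conditional. Modelling annual audits directly gives still lower power: at an assumed SD of 500 g and intracluster correlation 0.15, about 27% to 38% across illustrative splits of services by number of pre-intervention audits. But the Outcomes section says only that services have between one and three such audits. The split is not stated and Figure 1 is not shown, so those figures are not relied on here.

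Finally, the two perspective terms might be taken as a conflict over which costs count. Economic Evaluation, under its funders label, itself counts resource costs to the health system, and no cost item can be identified that would be treated differently. This is a wording difference only.

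**Conclusion.** The mismatch holds on the text alone: as written, the plan yields no cost-effectiveness ratio for the effect its second objective names. It is worth correcting, but it does not touch the primary comparison.

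The precision argument is secondary and conditional. Under an assumed birthweight SD of 400 to 600 g, power for a true 100 g difference is about 80% to 46%, against about 98% for a 5-point QCI change on the same basis. The sole ICER may therefore carry wide uncertainty. A reader might infer that it would be undefined or invalid. The figures do not support that: with a true effect of 100 g, a zero or negative estimate occurs in about 0.3% to 3% of trials over that SD range, and an ICER is an estimate to be reported with its uncertainty. If the precision argument is set aside altogether, the main point is unchanged.

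**What to change.** In the Outcomes section and in Economic Evaluation, add an incremental cost per QCI gain to the CEA. A natural unit is 5 points, the change that Sample Size describes as likely to be clinically significant. Keep the cost per 100 g of birthweight alongside it, worded the same way in both sections. Use one term for the perspective in both.

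No new data are needed, because the costs and the QCI are already inputs to the CCA. The cost is one more ratio to report, on a process measure that compares less readily with other programmes. Rewording the second objective to match the birthweight CEA would also remove the inconsistency, but would leave quality of care without a ratio.

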#### Implications and Significance

Despite growing international evidence, this study is the first to formally implement and assess in a cluster stepped-wedge design using quantitative outcome measures related to health care delivery, empowerment and health outcomes, the effect of applying a community participation intervention (PWG) to improve the quality of Indigenous MCH care in Australia. It brings together best practice in participatory approaches to strengthening health care with the expertise and reach of an experienced research collaboration to allow community members and health care providers to engage with MCH data from their community and implement changes to improve quality of care. Importantly (and often missing from previous research), the evaluation involves a cost-effectiveness analysis and a strong qualitative evaluation to learn how and why various components of the intervention exert any effects in various contexts. The economic evaluation also provides decision makers with evidence regarding the likely costs or cost-savings associated with wider roll-out of the intervention being tested.

Study outcomes will include: (i) refinement of a novel and scalable methodology with significant potential to engage community members and health care providers in MCH service improvement; (ii) development of a programme theory about mechanisms whereby PWGs exert their outcomes; (iii) direct transfer of findings to other Indigenous PHC services and to state and federal policy makers through well-established networks of knowledge exchange and partnership. Through this work the authors anticipate new knowledge of how best to facilitate improved quality of MCH care in Indigenous PHC settings and how to engage community members in driving health care improvements– this, in turn, will contribute to better intermediate health outcomes for women and babies and thus health outcomes for Indigenous Australians.

### Ethics and Dissemination

#### Ethical Approval

Ethical approval has been obtained through the Human Research Committee of the Northern Territory Department of Health and Menzies School of Health Research (ethics approval number is HREC 2018-3076); and James Cook University Human Research Ethics Committee (H7441). Additional ethical approval was obtained from the Western Australian Aboriginal Health Ethics Council (890) and the Aboriginal Health and Medical Research Centre Ethics Committee (1439/18). All eligible participants are required to provide signed informed consent before taking part in the study.

#### Data Management

All study related information is stored securely at the sponsor organization. All participant information is stored in a locked cabinet at the sponsor organization. All data sets are allocated an identification number to maintain participant confidentiality. Only study team members who are involved in data analysis have access to data.

Raw data are kept in a locked cupboard in the Principal Investigator's Office, and electronic data are stored on a password-protected computer. After the study finishes, electronic data will be transferred to a CD-ROM and also stored in a secure database repository and password protected. Electronic data on any other computers will be deleted. Raw data will be retained for at least 5 and 15 years respectively in accordance with NHMRC and the Australian Code for the Responsible Conduct of Research guidelines (51).

Participating services are involved in all decisions about data usage. No reference will be made in oral or written reports which could identify participants or the services without their written consent. None of these data, collected as part of this research, will be re-used without explicit permission. Raw data will be transferred to investigators involved in data analysis in other universities in accordance with protocols to safeguard data integrity.

#### Governance

The Steering Committee of the Centre for Research Excellence in Integrated Quality Improvement (CRE-IQI) is the overarching collaborative structure within which WOMB sits and consists of a broader network of Indigenous primary health care stakeholders. The CRE-IQI Steering Committee provides advice where required on the implementation of the actions devised by the PWGs, including the measurement of intermediate health outcomes and identify opportunities for broader roll-out and scale-up of study learnings.

The WOMB Steering Committee is responsible for monitoring conduct of the implementation, data collection and reporting. Committee membership comprises investigators, participant PHC services, facilitators of the PWGs and other members to be determined by the group. This group comprises members from the sponsoring organization and has no competing interests. It also assists in facilitation between the PWGs and their respective PHCs to implement action for mums and bubs; review and endorse interim reports; devise a knowledge transfer plan in phase 1 of the study; and assists with knowledge transfer activities throughout the life of the study.

Any protocol modification will be documented with appropriate justification and approved by the investigator team and steering committee. The final version will be presented to the relevant Ethics Committees, if required.

As the potential for harm based on this trial of women's group activity is extremely low, no formal stopping guidelines have been proposed. Ongoing process evaluation will ensure that any unanticipated unhelpful outcomes are identified and can be addressed.

#### Dissemination and Data Sharing

This study will be conducted in partnership with the PWG in each community, thus, overall results will be available for the PWG through existing auditing systems in the PHC services and a face-to-face visit to each service to present and discuss their own results overall. Interim progress reports will be made available to the steering committee of the CRE-IQI and study steering committee. The de-identified results of the research overall, across the ten services, will be made available to participating services through webinars, videos, and a face-to-face meeting.

This study will generate evidence about the effectiveness and cost effectiveness of community participation that is translatable to PHC settings in other Indigenous communities. Dissemination of findings to other Indigenous PHC services and to state and federal policy makers will occur through well-established networks of knowledge exchange and partnership; particularly through the networks of the CRE-IQI and through policy briefs and academic publication.

#### Trial Status and Protocol Version

Recruitment underway: Began April 2018 (services) and October 2018 (facilitators) and expect completion of recruitment approximately March 2020.

**Table d35e996:** 

April 2018 Original Version 1	
May 2018 Version 1.1	Primary reason for amendment – Ethical review process NT Health Ethics committee requested amendments to inclusion criteria to include women who are pregnant. Ethics committee review requested clarification on risk mitigation processes for participants
May 2019 Version 1.2	Primary reason for amendment- Modification of trial design from randomized to non-randomized. Statements were added and modified to improve clarity of trial design, participant inclusion and exclusion criteria and statistical methods.

## Data Availability Statement

The datasets generated for this study are available on request to the corresponding author.

## Abbreviations

ACCHS: Aboriginal Community Controlled Health Services
CCA: Cost-Consequence Analysis
CEA: Cost-Effectiveness Analysis
CQI: Continuous Quality Improvement
CRE-IQI: Centre for Research Excellence in Integrated Quality Improvement
EES: Emotional Empowerment Scale
FWB: Family Wellbeing Program
GEM: Global Empowerment Measure
ICER: Incremental Cost-Effectiveness Ratio
MCH: Maternal and Child Health
MCH QCI: Maternal and Child Health Quality of Care Index
PWG: Participatory Women's Groups
RSF: Remote Service Futures.
